### Arms

Intervention participants will download a telemedicine online/smartphone app (Nutrimedy, Brookline, MA, USA) and be connected at enrollment with a certified registered dietitian who will contact intervention participants weekly or bi-weekly via video calls and unlimited in-app text messaging for up to 3 months. The first week will include either one 55-min video session or two 25-min sessions. Weeks 2–4 will have weekly 25-min video calls, and weeks 5–12 will have biweekly 25-min sessions for a total of 8–9 sessions over 12 weeks. Together, participants and dietitians will come up with goals for the 12 weeks, and dietitians will check on progress toward these goals using in-app tools such as food logs and messaging between video calls. All patients will be encouraged to lose at least 20 pounds with a goal BMI < 40 kg/m^2^ after 12 weeks.

Dietitians will use principles of motivational interviewing, cognitive behavioral interventions, and the socioecological model to remotely provide behavior and lifestyle interventions. Motivational interviewing is a patient-centered, collaborative approach to counseling in which the dietitian elicits personally relevant reasons from subjects to make behavior changes that may promote weight loss. Dietitians and patients then structures goals for lifestyle modifications around these personal motivations [17]. Cognitive behavioral interventions provide subjects with strategies to change cognitive processes to alter behaviors, such as self-monitoring (e.g., recording food intake, weight, and exercise), stimulus control (e.g., keeping less healthy foods in cabinets out of sight), and accountability by having frequent check-ins with dietitians [18]. The socioecological model proposes that multiple levels of influence including intrapersonal (e.g., knowledge and attitudes), interpersonal (e.g., family and friends), and community factors (e.g., organizations, workplaces, neighborhoods) can impact energy-balance behaviors and weight outcomes [19]. Dietitians will promote the adoption and maintenance of behaviors across multiple levels of influence.

Individuals randomized to the clinical standard of care group will receive care according to current clinical guidelines. This may include a physical therapist and/or nutritionist referral, of which several programs within the institutions are offered to patients interested in weight loss, including the Nutrition Wellness Service (NWS) and Program for Weight Management (PWM).

### Blinding

Any staff involved in weighing participants or obtaining labs, as well as the principal investigator will be blinded from the group assignment until statistical analyses are finished. The subjects will not be blinded due to the nature of the study. While adverse events (AEs) are unexpected given the minimal risk of the study, if an AE potentially related to the intervention occurs, the principal investigator will decide whether the group assignment for a particular subject should be revealed.

### Surveys

All participants will complete a baseline survey at enrollment, and an end-of-study survey 10–14 weeks after enrollment (Additional files 1, 2 and 3). Questions about weight loss methods and the level of interest and confidence in weight loss were taken from Cleveland et al. [20]. Questions about motivation for weight loss were adapted from Meyer et al. [21]. Questions about exercise, diet, and goal setting routines were taken from the Paving Wheel Wellness score by Frates [22]. Items querying food frequency, hours spent doing physical activity, demographics, and opinions about the intervention were adopted from Seward et al. [8]. Alcohol and tobacco use questions were taken from the AUDIT-C alcohol screen and World Health Organization Global Tobacco Surveillance System [23, 24]. Surveys also included the Lower Extremity Activity Scale (LEAS) [25], PROMIS-Global Health scale, and the Knee injury and Osteoarthritis Outcome Score (KOOS) or Hip disability and Osteoarthritis Outcome Score (HOOS) depending on the joint [26, 27]. In addition to the demographic information collected on baseline surveys, we will also review each subject’s electronic medical record to obtain medication lists.

### Outcome measurements

Outcome and demographic data will be collected from blood serology, chart review, mobile app user data, pre- and postintervention surveys, and phone interviews.

#### Primary outcome measurement

The primary outcome will be weight change at 12 weeks (10–14 weeks) after study enrollment. Weights will be recorded at an onsite healthcare clinic or by home study scales.

#### Secondary outcome measurement

##### Weight and related measures

Weight-related secondary outcomes will include: percent weight (kg) change, BMI change, percentage of patients losing at least 20 pounds, percentage of patients eligible to undergo TJA by BMI < 40 kg/m^2^ at 3 months after study enrollment, number of weeks (up to 6 months) after enrollment until eligible for TJA by BMI < 40 kg/m^2^, number of dietitian calls until eligible for TJA by BMI < 40 kg/m^2^, and weight at 3-month post-operative visit when available. The percentage of patients undergoing TJA within 6 months of study enrollment will be calculated by review of each subject’s electronic medical record.

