However, despite multiple investigations regarding the association between lifestyle interventions and postoperative outcome, there is a dearth of research regarding success of weight loss interventions specifically prior to TJA. Although there are three studies of pre-operative dietary interventions prior to TJA, only one study concluded before surgery and this study did not compare pre-operative weight loss to a control group [12–14]. A 2015 review of nonsurgical, non-pharmacologic weight loss interventions in patients with obesity prior to TJA found that there was limited research on the association between weight loss prior to TJA and pre- and post-operative outcomes, and that future studies should address the safety, optimal timing, duration, amount of targeted weight loss, and delivery of pre-TJA interventions [15]. In addition, a recent study of patients about to undergo TKA or who were recently post-TKA found that patients wanted a weight loss program that started before surgery, was at least 6 months in duration, and focused on both diet and exercise [16].

In our proposed mixed-methods, multicenter randomized controlled trial (RCT), our primary aim is to assess the feasibility and efficacy of a 12-week RD supervised dietary and physical activity weight loss intervention and mobile app for patients with severe obesity prior to undergoing TJA. We hypothesize that a 12-week RD supervised dietary and physical activity weight loss intervention and mobile app for patients with severe obesity who are TJA candidates will result in (1) greater weight loss than clinical standard of care, (2) a higher percentage of patients eligible to undergo TJA by having a BMI below the standard cutoff of 40 kg/m^2^ within 3 months of enrollment, and (3) a higher percentage of patients undergoing TJA within 6 months of enrollment.

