### Eligibility criteria

#### Inclusion criteria

Subjects must be greater or equal to 18 years of age.Subjects must have 40 kg/m^2^ < BMI < 47 kg/m^2^ recorded in the electronic medical record within 6 months prior to enrollment. Weights recorded earlier than 2 weeks before enrollment must be verified by an additional weight measurement using study scales sent to subjects’ homes or in clinic during enrollment.Subjects must have end-stage knee or hip osteoarthritis, avascular necrosis, or rheumatoid arthritis with recommended primary, unilateral TJA by orthopaedic surgeons at two institutions.Subjects would consider undergoing TJA if eligible.Subjects own a smartphone, tablet, or personal computer compatible with video calls and a specified mobile app. The device must have a camera, access to Internet, and Apple App Store or Google Play.All subjects must be willing to comply with the requirements of the study and provide informed consent prior to enrollment. Evidence of a signed and dated informed consent document indicating that the subject (or a legally acceptable representative) has been informed of all pertinent aspects of the study must be obtained prior to data collection.

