#### Exclusion criteria

Subject’s enrollment BMI is less than 40 kg/m^2^ or greater than 47 kg/m^2^ when verified by study scale at subjects’ homes or by weight recorded at enrollment in clinic. BMI over 47 kg/m^2^ would require inappropriate weight loss of over three pounds per week to reach a BMI of 40 kg/m^2^ after 12 weeks.Subjects unable to comprehend and speak English.Subjects undergoing revision TJA.Subjects undergoing bilateral TJA.Subjects planning to undergo bariatric weight loss surgery in the next 6 months.Subjects planning to be pregnant in the next 6 months.Subjects unwilling or unable to use a smartphone, tablet, or personal computer with home Internet access.Subjects are incarcerated.Subjects are pregnant women or vulnerable individuals.

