### Patient population and recruitment procedure

Patients of fellowship trained arthroplasty surgeons at two institutions will be identified as potentially eligible for the study based on 40 kg/m^2^ < BMI < 47 kg/m^2^ recorded in the patient’s medical record within the last 6 months and recommended primary, unilateral total knee or hip arthroplasty. For patients identified as potentially eligible while in clinic, an orthopaedic surgeon will introduce the patient to the study, and a member of the research team (research assistant or trainee) will conduct an eligibility screening and obtain verbal consent either in-person or by phone. For patients identified as potentially eligible outside of clinic, a member of the research team will call the patient to introduce the study, and conduct eligibility screening and consent on the phone.

Eligible, interested, and consented patients will be provisionally enrolled, and all subjects will be shipped a standard bathroom scale to their home (Fig. 1). This initial enrollment is provisional, as subjects will be required to verify enrollment BMI by (a) submitting a photo to the study team of their study scale during a weigh-in that displays their body weight, or by (b) recording a baseline weight at an onsite healthcare facility within 2 weeks of provisional enrollment. Once enrollment BMI is verified to be 40 to 47 kg/m^2^, subjects will be fully enrolled and randomized to the intervention arm or clinical standard of care arm via REDCap. Subjects will be given a $40 check for enrolling, which includes (1) taking a baseline survey, (2) recording the baseline weight at an onsite healthcare facility or with a home study scale, and (3) getting baseline labs within 2 weeks of the baseline weight. Baseline weights will be recorded without shoes or outer clothing (e.g., coats). All subjects will be given a $20 check if they can verify a mid-study weight during week 6 of the study by recording a weight at any onsite healthcare facility or by submitting home study scale photos. All subjects will receive a $40 check for completing an end-of-study survey, weight, and labs at 10–14 weeks after enrollment.

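### The BMI < 40 endpoint shares its cut-point with the lower entry limit, so response depends steeply on baseline BMI; no adjustment is stated, and the article defines the endpoint in two ways

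*Protocol article*

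**What the plan says.** Entry and response share a boundary. Under Inclusion criteria, "Subjects must have 40 kg/m^2^ < BMI < 47 kg/m^2^ recorded in the electronic medical record within 6 months prior to enrollment". Under Patient population and recruitment procedure, "Once enrollment BMI is verified to be 40 to 47 kg/m^2^, subjects will be fully enrolled and randomized". Under Weight and related measures, one secondary outcome is the "percentage of patients eligible to undergo TJA by BMI < 40 kg/m^2^ at 3 months after study enrollment".

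The Background makes this hypothesis 2, in different words: "a higher percentage of patients eligible to undergo TJA by having a BMI below the standard cutoff of 40 kg/m^2^ within 3 months of enrollment".

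The article itself ties attainability to starting distance. Exclusion criteria explains the upper limit thus: "BMI over 47 kg/m^2^ would require inappropriate weight loss of over three pounds per week to reach a BMI of 40 kg/m^2".

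Randomization and allocation gives a 1:1 ratio in blocks of four and mentions no BMI stratum. Statistical analyses assigns t tests to continuous outcomes, and chi-square or Fisher tests to baseline characteristics and survey answers. It names no test for the BMI < 40 percentage and no covariate for any outcome.

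**The concern.** A patient at BMI 40.1 and one at BMI 47 count equally as responders once below 40. At 1.70 m (assumed), the first must lose about 0.3 kg and the second about 20 kg. A strong predictor of response is therefore recorded on everyone before randomisation, and nothing in the article says it will be used. With about 30 per arm, ignoring it costs precision on a named hypothesis.

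The two wordings are a separate difficulty. Weights are collected at week 6 and at 10–14 weeks. A patient below 40 at week 6 and above 40 at week 12 is a responder under the hypothesis and a non-responder under the outcome definition.

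**Working it through.** **1. The plan's own figure.** Sample size calculation gives mean changes of −3.38 and +2.01 kg (difference 5.39), SD 6.62 and 80% power. With two-sided 5%: n = 2 × (1.960 + 0.842)² × 6.62² / 5.39² = 2 × 7.849 × 43.82 / 29.05 = 23.7, so 24 per arm, as stated. No power is given for BMI < 40.

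**2. Response by baseline BMI.** Assume height 1.70 m (h² = 2.89) and normal weight change that does not depend on the starting value. For baseline BMI B and mean change μ:

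P(BMI < 40) = Φ([−(B − 40) × 2.89 − μ] / 6.62)

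| Baseline BMI | Loss needed (kg) | Intervention | Control |
|---|---|---|---|
| 40.5 | 1.4 | Φ(0.292) = 61.5% | Φ(−0.522) = 30% |
| 42 | 5.8 | Φ(−0.363) = 36% | Φ(−1.177) = 12% |
| 45 | 14.5 | Φ(−1.672) = 5% | Φ(−2.486) = 1% |
| 46.5 | 18.8 | Φ(−2.327) = 1% | Φ(−3.141) = 0.1% |

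From BMI 40.5 to 45, response in the intervention arm falls by about 57 points. The treatment difference is about 31 points at 40.5 and 4 points at 45. Height matters little here: at 1.68 m the figures for BMI 42 are 37% and 12%.

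**3. What drives response.** On the kg scale, with entry BMI even over 40–47 (variance 7²/12 = 4.08):
- baseline distance: 4.08 × 2.89² = 34.1
- treatment arm: (5.39/2)² = 7.3
- individual weight change: 6.62² = 43.8

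The shares are 40%, 9% and 51%. Over heights of 1.60–1.75 m and three assumed entry distributions (even, skewed toward 40, centred), they run 24–43%, 8–11% and 49–65%. For the yes/no response they are 11–20%, 4–7% and 74–82%. Baseline BMI outweighs arm, and individual change outweighs both.

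**4. Chance imbalance.** The SD of the between-arm difference in mean baseline BMI is 2.02 × √(2/30) = 0.52 for even entry. It is about 0.4 when entry is skewed toward 40. With even entry, a 0.5-unit upward shift moves the intervention rate from about 23% to 18%. The expected treatment difference is 23% − 9% = 14 points.

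**5. Power and test size.** These come from 20,000 simulated trials per setting, with 30 per arm and height mean 1.70 m, SD 0.09. Entry BMI is even over 40–47, or skewed toward 40 (Beta(1,2) over the range). Under no effect, both arms change by the average of the planning means, −0.685 kg. The adjusted tests come from logistic regression on arm and baseline BMI.

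| Test | Null rejection, even / skewed | Power, even / skewed |
|---|---|---|
| Chi-square, crude | 5.2% / 4.7% | 34% / 46% |
| Adjusted likelihood ratio | 6.3% / 5.8% | 44% / 55% |
| Adjusted score | 5.3% / 5.5% | 42% / 54% |

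Part of the likelihood-ratio gain comes from a liberal test. With its level set to 5%, power is 40% and 53%, a gain of about 6 points over crude chi-square. Across repeat simulations crude power is about 33–47%, the honest gain is roughly 5–8 points, and the likelihood-ratio test rejects about 6–7% under the null. Crude and adjusted mean risk differences agree (at 1.68 m: 0.146 and 0.145 with even entry, 0.227 and 0.230 with skewed entry), so the crude estimate shows no bias.

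**6. The two definitions.** The Background wording can be met by any qualifying weight up to 3 months; the outcome wording refers to status at 3 months. The rule carrying week-6 weights forward covers only a missing week-12 weight, so it does not reconcile them when both weights exist. Quality control and safety monitoring also asks intervention participants alone for weekly self-reported weights. The article does not say whether these could count. If they did, *within* would give that arm more chances to cross 40.

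**The case against.** The cut-point is the clinical question. Some surgeons use BMI 40 as their limit, so a patient who goes from 40.1 to below 40 does become eligible under it. Unequal required losses are already covered by threshold-free outcomes: weight change is primary, and BMI change and percent weight change are secondary. This stands, and the endpoint should be kept.

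The article names no test for this percentage, and a condensed article may leave the model to an analysis plan that is not shown. This also stands: that a crude comparison is planned is an inference, from the outcome being a percentage and from the unadjusted tests named for everything else.

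Randomisation protects the comparison, and an ordinary test's error rate already allows for chance imbalance. This is correct, so the loss is of precision and not of validity. The gain from adjusting is modest, and the endpoint stays underpowered either way.

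The sizes rest on assumed heights and entry distributions. The planning values come from a study that the Discussion describes as running over one year, with an unclear split of sessions before and after surgery. The percentages are therefore illustrative, but the steep gradient follows from the shared cut-point.

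The wording mismatch is small, and time to eligibility is a separate outcome. It still leaves one hypothesis with two definitions.

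**Conclusion.** The point holds as an efficiency and definition issue on a named secondary hypothesis. Response depends steeply on a baseline value that is verified before randomisation, and the article states neither a stratum nor a covariate for it. Under the planning values, crude power at 30 per arm is about 33–47%. Adjustment adds roughly 5–8 points at a true 5% level, depending on the assumed entry distribution. The *within* versus *at* 3 months contradiction needs no assumptions.

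Three stronger readings are tempting and are not supported:
- A reader might infer that response is determined mainly by baseline BMI. It outweighs treatment arm, but individual weight change is the largest component in every scenario examined.
- A reader might infer that a crude comparison would be biased. It would not.
- A reader might infer that patients enter on one noisy weight, so that many responders near 40 are artefacts. Record weights older than 2 weeks need an additional measurement. With even entry only about 0.2/7 = 3% of patients start within 0.2 units of 40, and such noise affects both arms alike.

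**What to change.** 1. Analyse BMI < 40 with baseline BMI as a covariate, and report a standardised risk difference beside the crude percentage in each arm. Use a score, penalised or permutation-type test: the ordinary likelihood-ratio test is slightly liberal at this sample size, and few control responders can cause separation.
2. Make the Background hypothesis and the outcome section agree on one definition, status at the verified 10–14-week weight. Keep time to eligibility as its own outcome.

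The cost is a sentence in the analysis section and one reworded hypothesis, with no new data. The downside is a model-based estimate beside the simple percentage, with some explanation for clinical readers. Neither change brings this endpoint to adequate power, so it is best read alongside BMI change.

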##### Feasibility and interactivity

The number of completed video call sessions with dietitians, number of food log uploads, and number of in-app messages sent to dietitians will be recorded by the mobile app.

##### Behaviors and function

Several behavioral and functional measures described previously will be assessed via surveys (Additional files 1, 2 and 3). When available, we will also review each subject’s electronic medical record to obtain standard clinical assessments including the PROMIS-Global Health scale, pain and function using Knee injury and Osteoarthritis Outcome Score (KOOS) or Hip disability and Osteoarthritis Outcome Score (HOOS).

##### Labs

Blood serologies measuring hemoglobin A_1c_, fasting blood sugar, fructosamine, insulin; serum albumin, pre-albumin, transferrin, total lymphocyte count; creatinine, and blood urea nitrogen (BUN); iron, folate, vitamin B12, serum electrolytes, and vitamin D will be recorded at baseline and end-of-study. Hemoglobin A_1c_, total lymphocyte count, albumin, and transferrin are highly recommended to evaluate nutrition status before orthopaedic procedures [28].

##### Qualitative

Intervention subjects at enrollment will be asked if they would be interested in completing a brief 5-min interview in-person or by phone at the end of the study (10–14 weeks after enrollment) to discuss qualitative feedback about the intervention. At the end of the intervention, interested intervention participants will be interviewed using an interview script (Table 1). Responses will be transcribed verbatim during the interview for later analysis.

**Table 1 Tab1:** Interview guide to be used for follow-up phone interviews with intervention subjects

	Domain	Question
1	Goals	What helped you achieve your goals during this study?
2	Motivation	What motivated you to achieve your goals?
3	Health Coach	How would you describe your experience with the mobile app and the dietitian?
4	Communication	What did you think about the different components for delivery of the intervention including video calls, phone calls, food logs, and the mobile app.
5	Communication	What did you think about the frequency of contact with dieticians?
6	Improvements	How would you improve the intervention?
7	Other	Any last comments about the intervention?

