### Statistical analyses

The main statistical analysis will be performed via an intention-to-treat analysis. Per protocol sensitivity analysis (completing at least half or four video calls) will also be performed. The significance level for statistical tests will be set at *p* ≤ 0.05. Baseline characteristics between the two groups will be assessed using t-tests for continuous variables and chi-square or two-tailed Fisher’s exact tests (when required by small cell counts) for categorical variables. Differences over time in continuous variables between the intervention and clinical standard of care group, such as percent weight change, body weight, and BMI, will be analyzed using *t* tests. Missing week 12 weight outcomes will be carried forward from week 6 outcomes when available.

We will measure feasibility via the ease of recruitment based on the ratio of enrolled subjects to the number of people approached about the study, and via maintenance of contact with a dietitian (e.g., number of video calls completed) based on study participant attrition and follow-up survey completion rates (retention). We will measure acceptability via survey items about components of the intervention, and through qualitative comments from a semi-structured interview. We will perform survey analyses using SAS (SAS Institute Inc., Cary, NC) or similar software. For most questions, participants will choose between four categories: strongly agree, somewhat agree, somewhat disagree, and strongly disagree. Assuming the distribution of responses to baseline surveys will be relatively similar, we will pool follow-up survey answers into “agree” and “disagree” for simplicity, and then conduct chi-square or two-tailed Fisher’s exact tests to examine differences between intervention and control group responses to follow-up surveys.

Qualitative data will be analyzed using the immersion crystallization method [29]. This qualitative technique includes multiple rounds of “immersion” through close readings of transcripts, followed by reflection and the “crystallization” of emerging themes. Multiple investigators will read the transcripts and arrive at a unanimous consensus concerning the emerging themes. Then, one investigator will code the transcripts to organize representative quotes.

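### The first two interview questions are worded as if goals were met, and none of the seven asks about barriers, so the Goals and Motivation themes will lean towards facilitators

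*Protocol article*

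**What the plan says.** Under Secondary outcome measurement, Qualitative, intervention participants are asked at enrollment whether they would be interested in a brief interview of about five minutes. Those interested are interviewed 10 to 14 weeks after enrollment with the guide in Table 1. It has seven questions.

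- Question 1 (Goals): "What helped you achieve your goals during this study"
- Question 2 (Motivation): "What motivated you to achieve your goals"
- Questions 3 to 7 cover the app and dietitian ("How would you describe your experience with the mobile app and the dietitian"), the delivery components, the frequency of contact, improvements ("How would you improve the intervention") and any last comments.

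The use of the answers is given under Statistical analyses: "We will measure acceptability via survey items about components of the intervention, and through qualitative comments from a semi-structured interview".

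The Arms section describes two kinds of goal. One is common to everyone: "All patients will be encouraged to lose at least 20 pounds with a goal BMI < 40 kg/m^2^ after 12 weeks". The other is individual: "Together, participants and dietitians will come up with goals for the 12 weeks".

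**The concern.** Question 1 asks what helped the participant reach goals without first asking whether they were reached. Question 2 has the same form, though it can also be read as asking about motivation to try. They open the guide, so a participant who fell short meets two prompts that do not describe their experience before reaching a neutral one. No later question asks what got in the way. Question 6 comes closest, but it asks how to change the intervention and not what hindered the participant.

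At stake is the balance of the qualitative results. Themes coded under Goals and Motivation will consist largely of facilitators, partly because only facilitators were asked for. In a trial of 30 per arm, the reasons why people fell short are among the more useful things an interview can yield, and they are hard to recover after the study has closed.

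**Working it through.** **Step 1. The wording of the seven prompts.**

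| Question | Presupposes success? | Asks about barriers or unmet goals? |
|---|---|---|
| 1 Goals | Yes | No |
| 2 Motivation | Partly | No |
| 3 Experience with app and dietitian | No | No, but open |
| 4 Delivery components | No | No, but open |
| 5 Frequency of contact | No | No, but open |
| 6 Improvements | No | Invites criticism of the intervention, not personal barriers |
| 7 Last comments | No | No, but open |

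Two of seven prompts carry the framing, and none of the seven names barriers.

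**Step 2. Inputs for the weight goal.** From Sample size calculation: expected change in the intervention arm -3.38 kg, SD 6.62 kg; usual care +2.01 kg; 80% power; 24 per arm, raised to 30. From Statistical analyses: significance level 0.05, taken here as two-sided. From Arms: goal of at least 20 lb, which is 20 × 0.4536 = 9.07 kg.

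**Step 3. Reproduce the plan's own figure.** Difference = 3.38 + 2.01 = 5.39 kg. With n per arm = 2 × (1.960 + 0.842)² × 6.62² / 5.39², the result is 23.7, rounded up to 24. This matches the article, so the mean and SD are being read as the planners used them.

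**Step 4. Share reaching 20 lb.** Assume normally distributed weight change:

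- z = (9.07 - 3.38) / 6.62 = 0.860
- P(loss of at least 20 lb) = 1 - Φ(0.860) = 0.195
- P(goal missed) = 0.805
- Of 30 intervention participants: 30 × 0.195 = 5.8, so about 6 reach the goal and about 24 do not
- P(no weight loss) = 1 - Φ(3.38 / 6.62) = 0.305

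**Step 5. Sensitivity of the share missing 20 lb.**

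| Assumed mean loss (kg) | Assumed SD (kg) | Share missing 20 lb |
|---|---|---|
| 3.38 | 5 | 87% |
| 3.38 | 6.62 | 80.5% |
| 3.38 | 8 | 76% |
| 5 | 6.62 | 73% |
| 7 | 6.62 | 62% |

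In each of these cases most participants miss the weight goal.

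**Step 6. What the figure does not cover.** The questions say only *your goals*. The Arms section has participants agree goals with the dietitian, and the Abstract describes these as concerning lifestyle changes. The article gives no attainment rate for them, so the share of interviewees whom the wording misfits cannot be computed.

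**The case against.** A reader might infer several stronger points that the article does not support.

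- **That the questions misfit four in five interviewees.** The 80% concerns the 20-lb goal only. A participant may meet agreed diet or activity goals without losing 20 lb. The planning values also come from a study that the Discussion describes as running over one year with an unclear number of pre-operative sessions, whereas this trial offers 8 to 9 sessions in 12 weeks. The objection stands, and the figure shows only that unmet weight goals should be expected.
- **That the interview as a whole is steered towards success.** Questions 3 to 7 are neutral, and an open question allows the answer that nothing helped. The article also calls the interview semi-structured, which leaves room for probes. This stands, so the point is limited to questions 1 and 2. Probing has little room, though: five minutes over seven questions is 300 / 7, or about 43 seconds each.
- **That feasibility is biased.** Statistical analyses measures feasibility from recruitment, completed calls and retention, none of which comes from Table 1.
- **That barriers go unrecorded in the trial.** Acceptability also rests on survey items. The surveys are in additional files not shown here and may ask about barriers.
- **That asking about interest at enrollment is a flaw.** Interest is recorded before any result is known. Moving the invitation to the end could let success or failure decide who volunteers, so there is no clear case for changing it.

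None of this removes the remaining point: the printed wording presupposes success, and no listed prompt balances it.

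**Conclusion.** The point holds as a minor one about wording. Question 1, and question 2 less strongly, assume that goals were met, and the guide has no prompt on barriers or unmet goals. The Goals and Motivation themes feeding the acceptability assessment will therefore lean towards facilitators. The reach is two of seven prompts. No quantitative outcome, test or efficacy conclusion changes.

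The supporting figure, about 80% missing the 20-lb goal, rests on normality and on the cited study's mean and SD applying at 12 weeks. Under the alternatives tried it ranges from 62% to 87%.

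**What to change.** In Table 1:

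- Reword question 1 to: *What helped, and what got in the way of, working towards your goals during this study?*
- Reword question 2 to: *What increased or reduced your motivation during the study?*

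Keep asking about interest at enrollment. When reporting the interviews, state how many interviewees completed at least four video calls and how many completed fewer. This uses the threshold already set for the per-protocol analysis and lets readers see how far less-engaged participants are represented.

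The cost is a minor amendment to the script. The call counts are already recorded by the app, so the added reporting needs no new data.
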